### Instruments and selected items used in the quantitative analysis

The questionnaires at T1 and T2 are both structured into five sections.

At both time points, we will examine the nature and severity of mental illness through self administered instruments resulting in discrete sumscores or subscale sumscores: the Patient Health Questionnaire (PHQ) [15], health-related quality of life (Short-Form 12, SF-12) [16], ability to work (work ability index, WAI) [14], burnout syndrome based on work-related stress (Maslach Burnout Inventory, MBI) [17], cognitive and emotional irritation (irritation scale, IS) [18] and working conditions (using the short questionnaire for work analysis, KFZA [19]).

At T1 we ask for demographic variables (age, gender, marital status, number of own children and the number of children in a household, educational and occupational status) as well as the number of previous contacts with the mental health care/psychotherapeutic system. The nature and frequency of previous psychotherapeutic treatments will be specified in months and standardized. The duration of the chief complaint will be recorded by the interviewer and also expressed in months.

The questionnaire of T2 has additional questions about the follow-up of the patient in the psychotherapeutic system, the implementation of the follow-up recommendations and patient satisfaction (ZUF-8) [20] (Table 1).

**Table 1 T1:** Target assessments and instruments

		**Time of implementation**	
**Target assessment**	**Instrument**	**T1**	**T2**
Demographic data	Individual items	x	
Previous contacts with the psychotherapeutic system	Individual items	x	
Work ability	WAI	x	x
Psychosomatic diagnosis, nature and severity of the illness	PHQ	x	x
Length of symptoms	Individual items	x	
Health-related quality of life	SF-12	x	x
Burnout syndrome based on work-related stress	MBI	x	x
Cognitive and emotional irritation based on work-related stress	IS	x	x
Working conditions	KFZA	x	x
Follow-ups in the psychotherapeutic system	Individual items		x
Patient satisfaction	ZUF-8		x

Overview of target assessments and corresponding psychometric instruments. For each instrument the time of implementation is indicated. T1 stands for baseline/before the intervention, T2 is defined as 12 weeks after T1.

### Statistical analysis

Research question 1 : *Are there differences in demographic, clinical and psychometric characteristics between patients who use the consultation offer in the workplace* versus *patients who use the established outpatient care?*

The differences between treatment groups will be examined by means of logistic regression analysis (in the form of binomial and multinomial models) including age, sex, educational level, occupational category, using the number of previous contacts with psychiatric-psychosomatic services as independent variables. The results of the logistic regression models will be used to estimate the propensity scores for the conditional probability of being referred to a particular treatment group.

The factors of interest of research question 1 are the type and severity of the disease (PHQ) the duration of symptoms, the health-related quality of life (SF-12), work ability (WAI), work-related stress effects (MBI, IS), work requirements (KFZA), the number of previous contacts with the mental health care system as well as demographic factors (Table 1). The demographics may be incorporated to the model independently or in terms of propensity scores.

By using multivariate analysis (latent class analysis = LCA) techniques it is possible to discern which patients with specific combinations of traits fit into certain clusters and determine the effect the particular setting has on the patients’ assignment in each particular cluster. The multivariate analysis is performed using the General Mixture Model (GMM) approach [21,22]. The basis here is the relationship between various characteristics of a limited number of categorical latent classes. The number of latent classes can be determined via various statistical methods (Bayesian Information Criterion, Akaike Information Criterion, Lo-Mendel-Rubin Test). By extending this model to a conditional latent class model, the effects of covariates on the likelihood of class membership can be estimated. The covariates in this study are the respective treatment settings, demographic data and job-specific characteristics of the responders.

Research question 2: *What are the changes 12 weeks after initially using the offer "psychosomatic consultation in the workplace" and how are they different from those in the control group?*

At time point T2, we will collect as primary outcome work ability (WAI). As secondary outcome we will collect the following target characteristics: type and severity of the disease (PHQ), health-related quality of life (SF-12), work-related stress effects (MBI, IS) and work requirements (KFZA). The main point of research question 2 is to detect whether or not there are significant differences between T1 and T2. The only newly collected data for T2 is patient satisfaction which will be analyzed descriptively. The effects of the setting on the change of the clinical characteristics will be analyzed by multivariate linear regression models with membership in the setting as independent variable and controlling for selection bias by including the propensity scores for the different treatment groups.

#### Qualitative analysis

The qualitative analysis will be performed by conducting expert interviews with representatives from three participatory groups (occupational health professionals, work councils and human resources professionals) within the companies. To qualify as an expert, the person would have to be involved in the implementation of the "psychosomatic consultation in the workplace." For both companies, this will yield about 3-5 experts per group and company.

The target characteristics and assessment method for research question 3: *What feedback is provided for persons involved with the offer for "psychosomatic consultation in the workplace" for the new model of care?*

We will use expert interviews to explore how the new offer is perceived. Expert interviews as a distinct form of semi-structured interviews are described by Meuser and Nagel (2002) [23,24]. Unlike the biographical interviews, the questions are not geared towards the personal traits of the interviewees but at their expert knowledge in their respective fields. The focus on the experts' status significantly and effectively limits the range of potentially relevant information that the respondent can provide [24].

The interviews are intended to encourage the experts to critically reflect on the implemented offer - the psychosomatic consultation in the workplace - and to report on their experiences, impressions and attitudes concerning changes in their respective company-supported health care systems. According to P. Mayring the texts will be transcribed and analyzed using qualitative content analysis methods. This technique will enable us to make inferences about the attitudes and impressions of the interviewees [25]. Text management will be supported by atlas.ti.

### Instruments

#### The work ability index (WAI) (short version)

The Work Ability Index (WAI) [14] is a quantitative instrument used to assess current and future work ability as well as work demand management based on behavioral measures. In our study, we are using the short version with 7 items. It has high reliability and validity.

#### Patient health questionnaire (PHQ), German version

The PHQ is an ideal and reliable tool to assess the most common mental disorders somatisation (15 items), anxiety (7 items) and depression (9 items) via self-assessment. The responses measure the frequency or the presence of symptoms with 2, 3 or 4 levels of severity. The interpretation of the PHQ is based on the diagnostic criteria of the DSM-IV and ICD-10, using a summative score between 0-30 with a 4-level severity scale of minimal, mild, moderate or severe. Patients who reach a cut off point of 10 or more are likely to require treatment. The PHQ is assumed to be objective because it is standardized in terms of its implementation and evaluation. The level of internal consistency for the continuous scale of the depression module is r = 0.88 and for the somatisation module it is r = 0.79. The test-retest reliability of the depression module lies between ICC = 0.81 and ICC = 0.96 (10). The criterion validity of the German version of the PHQ was identified as the “gold-standard” after being tested on 528 patients with reference to the "Structured Clinical Interview for DSM-IV”. The depression scale of the PHQ is also sensitive to change, making it a useful tool in longitudinal studies [15].

#### Health-related quality of life: SF-12

The SF-12 is the validated short version of the SF-36, an instrument that measures the health-related quality of life of patients. The 12 individual items record 8 dimensions, which can be conceptually sorted in terms of "physical health" and "mental health." The calculated scores can reach values of between 0 and 100 points, with low values reflecting poor health and higher values indicating better health [16].

#### Maslach Burnout Inventory (MBI), German general version (MBI-GS-D)

The MBI is used to assess burnout syndrome as a manifestation of mental exhaustion [17]. Although it overlaps with the depressive syndrome (ICD-10), it demonstrates a useful model of cause and effect. The phenomenon of burnout was first described in the helping professions. In the present study, we use the general version, which has been validated with 16 items (MBI-GS-D). Thus, the method allows a diagnosis of the three components of burnout: emotional exhaustion (EE), depersonalization (DP) and (reduced) personal accomplishment (PA). The items are classified according to frequency. These were tested and validated in several business sectors and occupations.

#### The irritation scale (IS)

Irritation is defined as a subjectively perceived emotional and cognitive strain in occupational contexts. The Irritation Scale, in particular, is recommended for application in occupational contexts. It can be used for evaluating interventions, research on stress at work, and individual counselling. In addition, irritation has been shown to be a precursor to other impairments. The irritation scale is a subjective tool with proven reliability and validity [18].

#### KFZA: analyzing work requirements (KFZA)

The KFZA is a method of determining working conditions. We used the short form based on the selection of 26 items from the long version. This is a time-efficient and subjective screening instrument to detect positive and negative influences of industrial and organizational structure. The results include aspects of work content, resources, stressors and the organizational climate and yield information about health promotion programs [19].

#### Patient satisfaction (ZUF-8)

The ZUF-8 (created by J. Schmidt, F. Lamprecht and W. Wittmann) is a method for globally detecting patient satisfaction with confirmed reliability and validity. It consists of eight items that have four answer choices without a "neutral" position. The individual items also have face validity. The answers each have a value of 1 to 4. Four of the eight items (items 1, 3, 6 and 7) are pooled negatively. After reversing the negatively poled items, the scores of all eight items are added (summative scores range from 8 to 32). High summative scores indicate high patient satisfaction, and vice versa [20].

### Inclusion criteria

The only inclusion criterion is that the respondents must be at least 18 years of age. Other inclusion criteria are not relevant since we are recruiting consecutively and this is an explorative study.

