Currently, little is known about the profile of utilizers, or about the effects of this new model of care. Therefore, our study aims to assess the following research questions:

1. Are there differences in demographic, clinical and psychometric characteristics between patients who use the consultation offer in the workplace versus patients who use conventional outpatient care? Is this new model of mental health care successful in reaching employees suffering from psychological disorders earlier in the course of their illness, compared to patients who seek help in conventional outpatient care?

2. What changes occur within a three-month follow-up period after using the offer "psychosomatic consultation at the workplace"? Are they different from those of a conventional outpatient clinic?

3. What is the feedback (i.e. appraisals, attitudes, criticism) of persons who are involved with the offer "psychosomatic consultation in the workplace"?

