### Sample size and power calculations

Statistical power analyses was conducted with regard to the work ability index (WAI) [14] as primary outcome. In our regression model we assume that the condition „intervention in the workplace/in the psychosomatic clinic“explains a variance of 5%. This means that at a statistical significance of 5% and a power of 95%, we will need 110 participants in each group (workplace and clinic) with a total sample size of n = 220. Bearing in mind a drop out rate of 20% we will include 280 patients.

The quantities for the main question (research question 1) in this explorative study result from the foreseen time schedule during the funding period and the feasibility of recruitment. We expect a high rate of participation since the "psychosomatic consultation in the workplace" so far has been greatly accepted and appreciated by the employees. In addition, the employees are assured that the collected data will be kept confidential under the supervision of the research group at the university. To increase the response rate for the follow-up survey, there will be a reminder mailing or a phone call.

There are 14 variables to be measured. The two intervention groups consist of employees who use this service within the 10 month recruitment period. One company has a total of 70,000 employees at the participating sites. The other company has about 3,000 employees. The ratio of male to female employees in both companies is about 4:1 with an average age of 43 years. The employees are unevenly distributed to work in research, development, production and administration.

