### Relevance of the study

A lack of easy accessability, as well as stigmatisation of the mental health care system [26], obstructs help-seeking behavior. In Germany, 50% - 90% of individuals with psychosomatic disorders do not manage to obtain professional care, as a recent report on behalf of the National Association of Statutory Health Insurance Physicians (KBV) revealed [27,28]. These aspects, among others, may contribute to the chronification of common mental disorders such as depression, anxiety and adjustment disorder, as well as functional somatic disorders. Therefore, common mental disorders should be treated within the early stages of onset, as they are known to be especially responsive to treatment during the early phases of illness [29]. In addition, a recent study showed that even if the employees’ home life is stressful, tackling workplace stress is likely to improve employees’ psychological health [30]. These facts validate the need for brief, easily accessible and tailored interventions at the workplace.

With the model “psychosomatic consultation in the workplace,” we aim to offer an integrative, timely and easily accessible first consultation to affected employees. The stigma of mental disorder is intended to be minimized by bringing the psychosomatic consultant to the patient instead of vice versa. Furthermore, the psychosomatic consultation is embedded within occupational health facilities at the workplace. These aspects are likely to make the consultation at the workplace an instrument to reduce chronification.

In this study, we will describe the utilizers of a new model of mental health care in the workplace. This model follows numerous other concepts of work-related programs, such as return to work interventions [31,32], stress prevention training [9,33,34] and interventions for healthy management [35,36]. “Psychosomatic consultation in the workplace” addresses those workers and employees who still have the ability to go to work. It focuses on improving work ability of affected individuals, and hence, can be regarded as a form of secondary and tertiary prevention.

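### Employment is fixed in the workplace groups but uncontrolled in the clinic groups, which confounds setting with employment in the between-setting work-ability comparison and the reached-earlier question

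*Protocol article*

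**What the plan says.** The Inclusion criteria section sets one rule, "The only inclusion criterion is that the respondents must be at least 18 years of age", and gives its reason: "Other inclusion criteria are not relevant since we are recruiting consecutively and this is an explorative study".

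On the workplace side, the section on sample size and power says: "The two intervention groups consist of employees who use this service within the 10 month recruitment period". The section on the study's relevance adds that the offer "addresses those workers and employees who still have the ability to go to work". No section shown sets an employment condition for the clinic patients.

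Two comparisons depend on this:

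- **Research question 2 (Statistical analysis):** "At time point T2, we will collect as primary outcome work ability (WAI"). The effect of setting on change is estimated by linear regression, "controlling for selection bias by including the propensity scores for the different treatment groups". Burnout (MBI), irritation (IS) and working conditions (KFZA) are among the secondary outcomes. Of the irritation scale the article says: "Irritation is defined as a subjectively perceived emotional and cognitive strain in occupational contexts".
- **Second part of research question 1 (Background):** whether the new model succeeds in "reaching employees suffering from psychological disorders earlier in the course of their illness, compared to patients who seek help in conventional outpatient care".

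The covariates named for the propensity model are age, sex, educational level, occupational category and number of previous contacts with services. Occupational status is recorded at T1 (Instruments and selected items).

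**The concern.** Having a job is a condition of entering one arm and is left open in the other. Consecutive outpatients may include people who are unemployed, retired or studying. The primary outcome and three secondary scales concern work, so a between-setting difference in their change could partly reflect employed versus non-employed patients and not the place of consultation.

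The same holds for symptom duration. The research question speaks of employees, but the comparator is all clinic patients. If non-employed clinic patients have had symptoms for longer, the workplace offer would seem to reach people earlier even if employed patients came to both settings at the same stage.

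The planned adjustment helps only in part. The article does not say whether occupational category has a level for people without a job. If it does, nobody at that level can be in the workplace arm, and a regression that includes them extrapolates.

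**Working it through.** **Inputs from the protocol article**

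- Setting explains 5% of variance; significance level 5% (sidedness not stated); power 95%; 110 per group, 220 in total; 20% dropout; 280 recruited (Sample size and power calculations).
- 70 patients in each of four settings (Abstract), so 140 workplace and 140 clinic patients.

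**Assumptions, not in the documents**

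- Share *u* of clinic patients without a job: 20% to 40%.
- Difference *g* in WAI change between clinic patients without and with a job: 0.5 SD.
- The planned effect is read on the same SD scale as WAI change.

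**Step 1. Planned effect in SD units.** f² = 0.05 / 0.95 = 0.0526. For two equal groups, d = 2 × √0.0526 = 0.459.

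**Step 2. The plan's own sample size.** A two-sided test at d = 0.459 with 110 per group has 92.3% power (two-sample t test). 95% power needs about 124 to 125 per group. A one-sided test needs 103 per group, or 109 if the 5% is entered as f² itself; the latter is close to the stated 110. The unstated sidedness is a separate matter. Two-sided power is used below. For dropout, 220 / 0.8 = 275 against the stated 280, and 280 × 0.8 = 224 completers, or 112 per group.

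**Step 3. Shift if non-employed clinic patients answer the WAI and are analysed without adjustment.** Shift = *u* × *g*.

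| *u* | Shift (SD) | Share of 0.459 |
|---|---|---|
| 20% | 0.2 × 0.5 = 0.10 | 22% |
| 40% | 0.4 × 0.5 = 0.20 | 44% |

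The sign depends on which patients change more, which is unknown.

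**Step 4. Effect on the test if setting has no effect.** SE = √(2/112) = 0.134 SD. The shift is 0.10 / 0.134 = 0.75 or 0.20 / 0.134 = 1.50 standard errors. A nominal 5% two-sided test then rejects in about 12% or 32% of trials (normal approximation).

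**Step 5. Power if only employed clinic patients are compared.** Clinic completers = 112 × (1 − *u*), rounded down; workplace completers stay at 112; d = 0.459; two-sided t test.

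| *u* | Clinic completers | Power |
|---|---|---|
| 0% | 112 | 92.8% |
| 20% | 89 | 89.5% |
| 40% | 67 | 84.0% |

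**The case against.** **Unlike populations are the object of study.** The sample size section calls research question 1 the main question, and the Discussion gives the main objective as identifying types of patients by setting. Under Strengths and weaknesses, consecutive recruitment without matching on age, gender or severity is a deliberate choice. This stands for the description of users: a difference in employment is a finding there, and the entry criterion need not change. It does not cover the between-setting contrast on a powered outcome, or a question worded about employees.

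**The plan already handles part of it.** Occupational category is in the propensity model, and job-specific characteristics are covariates in the latent class model. This stands in part; how far employment is captured is not stated.

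**Restriction does not restore overlap.** A reader might infer that the propensity score fails only because of people without a job, and that removing them repairs it. That is not so. The workplace patients come from two companies, and an employed clinic patient who works elsewhere also could not have used the workplace offer. Restriction makes the groups more alike and no more than that.

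**The mechanism is unsettled.** A reader might infer that the WAI cannot be answered without a job. The article gives no WAI items and describes the index as covering current and future work ability, so this is not shown. If the WAI were missing for these patients, they would drop out of a complete-case model. The cost would then be the power loss in Step 5, not the shift in Step 3.

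**The size is assumed.** Neither the share nor the 0.5 SD comes from the documents. Research question 2 concerns change, so a difference in baseline level alone would not produce the shift. Step 3 also ignores the planned adjustment. All of this stands.

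**Two further inferences are unsupported.** That every workplace patient is still at work goes beyond the text, which describes whom the offer addresses and sets no entry rule. That patients might be enrolled in both arms is not shown by the sections cited here.

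**Conclusion.** The concern holds in a limited form. The imbalance follows from the text: employment is certain in the workplace groups and open in the clinic groups. It matters for the between-setting comparisons of WAI change and the other work-related scales, and for the symptom-duration comparison. It does not matter for the description of users or for the change from T1 to T2 within the workplace groups.

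The size is unknown. The 22% to 44% of the planned effect illustrates an unadjusted contrast under an assumed 20% to 40% non-employed share and an assumed 0.5 SD difference in change. With a share near zero there is almost no bias, and restriction costs almost nothing.

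A reader might infer that the trial cannot answer research question 2 at all, or that the entry criterion is an error. The documents support neither. This is an analysis-set choice worth correcting because it is cheap, and it does not invalidate the design.

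**What to change.** Keep age 18 or over as the entry criterion and keep all consecutive patients for the description of users. Add one sentence to the Statistical analysis section: for the between-setting comparisons under research question 2 and for the symptom-duration comparison, the analysis set is patients in employment at T1, identified from the occupational status already recorded; the same analyses in all patients are reported as a sensitivity analysis. Report the number of non-employed patients in each clinic so that readers can judge how much this matters.

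No new data and no extra recruitment are needed. The costs are a smaller clinic analysis set (89 or 67 of 112 completers at the assumed 20% or 40%, with the power in Step 5) and results that apply to employed patients only. The text should also say that employed clinic patients from other companies could not have used the workplace offer, so some lack of overlap remains.
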